### Data Collection

Data collection will take place at baseline (the day of the intake meeting), immediately before and after the MBI, and at the end of the 6-month study period, as detailed in Table 1.

All participants will provide background information at intake including age, birthdate (month/year), grade at school, past medical history, medication, and previous exposure to contemplative sciences (including yoga, meditation, and mindfulness). Participants will provide data through research questionnaires and salivary cortisol as well as individual semistructured interviews with the research assistant as detailed in Table 2. Participants will also provide information about individual practice using electronic participant logs during the 8 weeks of the MBI and when completing research questionnaires at the end of the sixth month of the study period. Data from research questionnaires and participant logs will be collected via the TickIT platform (GASQ Service GmbH), a youth-friendly, secure, digital assessment platform, via computer, tablet, or mobile phone [32]. Data compilation will take place through the TickIT platform as well.

**Table 2 table2:** Summary of primary and secondary outcome measures.

Outcome	Measurement	Description	Length
Mindfulness skills acquisition (primary outcome)^a^	Mindful Attention Awareness Scale for Adolescents (MAAS-A) [41]	14-item scale evaluating level of mindfulness as a quality of attention informed by an awareness of the present experience	Approximately 3 min
Illness perception^a^	Illness Perception Questionnaire (brief) [47]	9-item measure of health-related quality of life for adolescents including those with acute and chronic health conditions. Provides an overview of how the illness is affecting overall level of functioning	Approximately 3 min
Mood and anxiety^a^	Depression Anxiety Stress Scale (DASS-21) [48]	21-item scale assessing mood and anxiety symptoms in adolescents based on self-evaluation of symptoms in the past 7 days	Approximately 5 min
Self-esteem^a^	Rosenberg Self Esteem Scale [49]	10-item scale assessing self-esteem and overall satisfaction with life	Approximately 3 min
Stress (biological marker)	Salivary cortisol levels [42]	Self-collected saliva samples using cotton swabs (Salivettes). Analysis by immunoassay	1 minute per sample
Individual practice	Data reported in participant log books	Participants will be encouraged to detail individual home practice in a digital log book noting frequency, duration, and type of practice	Approximately 5 min per week
Participant appreciation	Verbatim transcription of semistructured interviews	Individual interviews with study participants will be conducted at the end of the 8-week MBI^b^ using the Zoom eHealth platform	15 to 30 min
Facilitator feedback	Data reported in facilitator log books	Facilitators will use pre- and postsession log books to detail impressions and adaptations of the MARS-A^c^ program for the eHeath platform	Approximately 15 min per entry

^a^All measurement scales included in this table have been validated in clinical youth populations and have shown favorable psychometric profiles (Cronbach alpha>.80).

^b^MBI: mindfulness-based intervention.

^c^MARS-A: Mindful Awareness and Resilience Skills for Adolescents.

All interviews will take place through the Zoom electronic audio-visual platform and will be led by a female research assistant, coauthor CV (MD). The research assistant will use an interview guide adapted from a study led by coauthor SAK [33]. She will be encouraged to take field notes during the interviews and will have received individual training in conducting semistructured interviews by coauthors EW (MEd) and SAK (PhD), who both have experience leading semistructured interviews and focus groups with youth. Participants will complete the interview in a private room, at home, with no other nonparticipants or researchers present and will be informed that the research assistant is a medical doctor, has limited experience with mindfulness, and has interest in understanding the effects of mindfulness in adolescents with chronic medical conditions. The research assistant will have met with each participant at baseline either in-person or virtually through the Zoom platform for a recruitment meeting. Recordings will be password-protected and only the research assistant (who will also be transcribing the recordings) will have access to them. Transcriptions will be de-identified using a patient code available only to the research assistant. Transcripts will be returned to participants for comment and correction if there is ambiguity at the time of analysis. Data will be analyzed using a grounded theory model [34] until data saturation is reached. Data for secondary outcomes will be collected for all participants. It is expected that research questionnaires will take 15 to 20 minutes to complete.

Saliva samples for cortisol analysis will be drawn at wake-up, at 12:00 PM, at 5:30 PM, and at 7:00 PM on the first and eighth (last) MBI session to capture fluctuations in cortisol levels throughout the course of the day. Participants will receive a reminder phone call the day before each saliva sampling occurs. This will allow for the comparison of pre-post cortisol level differences between participants in the in-person and eHealth arms. Participants in the eHealth arm will be provided with prepaid postage for return of saliva samples, which they will be able to send from home. It has been shown that saliva samples can be exposed to room or exterior temperatures for at least 72 hours without affecting cortisol values [35]. Once received, saliva samples will be kept frozen until they are sent to a specialized laboratory for analysis by enzyme immunoassay [36].

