### Recruitment and Enrollment

Recruitment for this study will primarily take place in outpatient clinics of a tertiary care pediatric hospital when patients arrive for their scheduled initial or follow-up appointments. Participants will be referred for inclusion in the study by a member of their health care team after discussion with the patient and family. Nurse practitioners and social workers will also screen clinic lists to proactively identify potentially eligible participants. Brief presentations of the study will occur at divisional rounds and with small groups of health providers to increase awareness about the study. Posters and brochures will be distributed throughout clinics and offices.

Recruitment will occur until a convenient sample size of 60 participants is reached or until a maximum of 3 months of active recruitment has occurred (whichever happens first). Based on the results of a pilot study performed by our research team with 19 female adolescents with chronic pain [15], we anticipate that a period of 3 months will be sufficient to enroll the targeted number of participants (average enrollment rate: 5 participants per week).

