**Figure 1 figure1:**
[figure not shown]
Experimental design of a randomized longitudinal trial comparing in-person versus eHealth delivery of an 8-week mindfulness-based intervention for adolescents with chronic illness.

**Table 1 table1:** Overview of data collection.

Time point/group	Baseline	Time 0	Week 8	Week 16	6 months
Early groups: experimental arm (distance or eHealth). MBI^a^ begins at time 0.	Background data; Research questionnaires	Salivary cortisol; Participant and facilitator logs (weekly for 8 weeks)	Salivary cortisol; Research questionnaires; Semistructured interviews	Research questionnaires	Research questionnaires
Wait-list control groups: experimental arm (distance or eHealth). MBI begins at week 8.	Background data; Research questionnaires	—	Salivary cortisol; Research questionnaires; Participant and facilitator logs (weekly for 8 weeks)	Salivary cortisol; Research questionnaires; Semistructured interviews	Research questionnaires

^a^MBI: mindfulness-based intervention.

At the end of the recruitment period, once eligibility criteria have been verified, randomization will take place to separate participants in the 4 different groups within the in-person and eHealth arms of the study.

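### Table 1 gives the early groups no questionnaires at MBI start, so their last pre-MBI MAAS-A is about 6 weeks old on average and up to 12–13, while the wait-list groups are measured as they start

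*Protocol article*

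**What the plan says.** The Data Collection section sets the general schedule: "Data collection will take place at baseline (the day of the intake meeting), immediately before and after the MBI, and at the end" (the last point being month 6). Intake and the point just before the MBI are named as separate occasions, and Table 1 is cited for the detail.

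Table 1 defines the two kinds of group as follows.

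- Early: "Early groups: experimental arm (distance or eHealth). MBI^a^ begins at time 0". The time-0 cell reads "Salivary cortisol; Participant and facilitator logs (weekly for 8 weeks"). Research questionnaires appear at intake and next at week 8, after the MBI.
- Wait-list: "Wait-list control groups: experimental arm (distance or eHealth). MBI begins at week 8". The week-8 cell reads "Salivary cortisol; Research questionnaires; Participant and facilitator logs (weekly for 8 weeks"). These groups therefore have questionnaires both at intake and at MBI start.

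On timing, the Study Design section states: "At the end of the recruitment period, once eligibility criteria have been verified, randomization will take place". Under Recruitment and Enrollment, recruitment continues to 60 participants or "until a maximum of 3 months of active recruitment has occurred (whichever happens first"), at an expected average of 5 participants per week.

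The primary outcome, the MAAS-A, is one of the questionnaires. The Data Analysis section plans paired t tests, analyses of variance and analyses of covariance for pre-post MBI change, for in-person versus eHealth and for early versus wait-list. It does not say which score counts as the pre-MBI score.

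**The concern.** A pre-post test of an 8-week program needs a score taken close to the start of the program. For the wait-list groups Table 1 provides one. For the early groups, half of the target sample, the only score before the MBI comes from the intake meeting, which may lie weeks or months earlier.

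Two things follow. First, pre-post change in the early groups contains whatever happened between intake and the first session, including natural drift and regression to the mean. If early and wait-list participants are analyzed together, the word pre has two meanings. Second, an older score is likely to correlate less with the post-MBI score, which costs precision in a trial of only 60. The DASS-21 shows the problem most plainly: it asks about the past 7 days, so an intake answer says little about the state at a session many weeks later.

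An analysis plan cannot repair this, because a score that was not collected cannot be recovered.

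**Working it through.** **Inputs from the protocol article**

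- Target 60 participants, 5 per week, at most 3 months (Recruitment and Enrollment).
- Randomization after recruitment closes (Study Design).
- MBI start at time 0 (early) or week 8 (wait-list); MBI length 8 weeks (Table 1).
- 15 early and 15 wait-list participants targeted in each arm (Study Design).

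**Assumptions, not in the article:** even enrollment over time, and a gap of 0 to 4 weeks between randomization and time 0.

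**1. The plan's own figure.** Time to enroll = 60 / 5 = 12 weeks, about 2.76 months. This agrees with the stated 3 months (about 13 weeks).

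**2. Age of the last pre-MBI questionnaire in the early groups.** Age at MBI start = (close of recruitment − intake date) + gap.

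- Gap 0: maximum 12–13 weeks; mean 12/2 to 13/2 = 6–6.5 weeks.
- Gap 4: maximum 16–17 weeks; mean 10–10.5 weeks.

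In the wait-list groups the week-8 score is 0 weeks old at MBI start.

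**3. Pre-post interval** = age + 8 weeks.

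| | Mean | Maximum |
|---|---|---|
| Early, gap 0 | 14–14.5 weeks | 20–21 weeks |
| Early, gap 4 | 18–18.5 weeks | 24–25 weeks |
| Wait-list, from week 8 | 8 weeks | 8 weeks |

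Using intake for everyone does not remove the problem. The wait-list interval from intake to week 16 would then be 6 + 16 = 22 weeks on average, and up to 13 + 16 = 29, with gap 0.

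**4. Which comparisons are affected.** The age of the intake score is fixed before allocation, and each arm has the same early/wait-list split. The mean drift contained in the change scores is therefore expected to be the same in the in-person and eHealth arms and to cancel in their difference. Early versus wait-list at week 8 can use the intake score in both groups, which is symmetric. What remains affected is change within groups.

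**5. Precision, illustration only.** The article gives no pre-post correlation r. With equal variances before and after, SD of change = SD × √(2(1 − r)).

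| r | SD of change / SD |
|---|---|
| 0.7 | 0.775 |
| 0.6 | 0.894 |
| 0.5 | 1.000 |
| 0.4 | 1.095 |

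If the lag lowered r from 0.6 to 0.4, the SD of change in the early groups would rise from 0.89 to 1.10 times the raw SD. If it did not lower r, nothing would be lost.

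**The case against.** The strongest objection is to the wording. The Data Collection sentence speaks of data in general and leaves the detail to Table 1. Saliva is collected from the early groups at time 0, so the sentence is literally met. That stands: a reader might infer that the text promises questionnaires at time 0, and it does not say so outright. But the sentence separates the pre-MBI occasion from intake, and Table 1 applies it to questionnaires in the wait-list groups only. For the primary outcome the schedule is uneven.

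A reader might also infer that the primary noninferiority result is biased. The documents do not support this, because the early/wait-list split is the same in both arms. Nor is early versus wait-list necessarily distorted, for the reason given under step 4.

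A third tempting step is a large loss of power in the analysis of covariance. If r fell from 0.7 to 0.5, residual variance would go from 1 − 0.49 = 0.51 to 1 − 0.25 = 0.75, which is 47% more. Both correlations are assumed, and the figure treats every participant as having an old score. If half do, the average is (0.51 + 0.75) / 2 = 0.63, about 24% more; with no fall in r it is 0%. The article also does not say that the primary comparison adjusts for the score nearest to the MBI.

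Finally, a baseline taken before allocation is a defensible choice. A time-0 answer comes after participants have been told their group by phone. This is a reason to keep the intake score for the randomized comparisons, but it does not supply a start-of-MBI score for pre-post change. Figure 1 is not available here, so the reading of the schedule rests on Table 1 and the text.

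**Conclusion.** The point holds for pre-post change. As scheduled, the early groups have no MAAS-A or other questionnaire at MBI start and the wait-list groups do. The early groups' last score is about 6 weeks old on average and up to about 12–13 weeks, and more if there is a gap before time 0. The 21-week interval applies only to someone enrolled at the very start of a full 3-month recruitment; about 14 weeks is typical.

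These figures rest on the stated enrollment rate, even enrollment and no gap. The contrast with 8 weeks assumes that the week-8 score serves as the wait-list groups' pre-MBI score, which the article does not specify. Any loss of precision cannot be sized from the article. The consequence is a blurred reading of the within-group effect of the MBI. It is not evidence against the noninferiority comparison. The change is worth making because it is cheap.

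**What to change.** 1. Reconcile the Data Collection section with Table 1 by adding the questionnaires at time 0 for the early groups, at least the MAAS-A.
2. Define the pre-MBI score for pre-post change as the one at each group's own MBI start: time 0 for early, week 8 for wait-list. The interval is then 8 weeks in all four groups.
3. Keep the pre-randomization intake score as the covariate for both randomized comparisons, in-person versus eHealth and early versus wait-list.
4. The Results section says that data collection is underway. For any early group that has already started, report the distribution of the intake-to-start interval and interpret its pre-post change as covering that interval too.

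The cost is an amendment to Table 1 and one more online questionnaire on the existing platform for the early groups: about 3 minutes for the MAAS-A alone, or 15 to 20 minutes for the full set. The time-0 answers are given after allocation is known, so they should not replace intake in the randomized comparisons. For the same reason, the change makes pre-post change clearer but does not add precision to comparisons adjusted for intake.

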Participants in the in-person groups will meet at the hospital in a designated teen-friendly room containing chairs and yoga mats. Sessions will take place once a week after school from 5:30 PM to 7:00 PM. Participants will have a 5-minute break at the middle of each session, and a snack will be provided.

Participants in the eHealth groups will be encouraged to find a quiet room with as little outside noise and distraction as possible. They will be required to have access to the Internet, a desktop or laptop computer equipped with a webcam or a tablet or mobile phone with webcam function. Participants and facilitators will be connected using the secure password-protected audio-visual platform Zoom Video Conferencing allowing up to 50 different computer connections. With this interface, participants and instructors can see and hear each other and interact in real time. This interface also allows for audio and video recording of mindfulness sessions and allows hosts to restrict access to meeting members who might not behave appropriately during sessions. All in-person and eHealth mindfulness sessions will be recorded and reviewed by a clinical psychologist with experience and expertise in mindfulness for adolescents (coauthor CMH) to ensure delivery of similar content between groups.

**Table 3 table3:** Thematic overview of the Mindful Awareness and Resilience Skills for Adolescents curriculum.

Week	Theme	Content
1	Stress, Depression and Health—Introduction to Mindfulness for Adolescents	Introduction to mindfulness and group expectations Introduction to stress and depression Group and home practices: breathing practice, sitting meditation, and the body scan
2	Foundations of Mindfulness	Developing a practice Key elements of mindfulness Group and home practices: body scan, mindful eating, sitting meditation
3	Informal Mindfulness Practice and Gratitude	Introduction to informal mindfulness practice Gratitude and pleasant events Group and home practices: mindful movement, 3-minute breathing space, walking meditation
4	Unpleasant Experiences, Physical Sensations, Physical Pain	Discussion: making peace with pain, suffering, and unpleasant physical sensations Group and home practices: mindful stretching, 3-minute breathing space, body scan
5	Seeing Thoughts as Thoughts	Cognitive exercise: thought distortions Discussion: mindfulness of thoughts, rumination Group and home practices: sitting meditation, short breathing practices

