### Outcome Measures

The primary outcome measure for this study is mindfulness skills acquisition, assessed by the Mindful Attention Awareness Scale for Adolescents (MAAS-A) [41]. This 14-item Likert-type scale has been previously validated in large samples of youth with chronic health conditions. Secondary outcomes will include quantitative and qualitative measures as detailed in Table 2: illness perception, mood and anxiety, self-esteem, cortisol levels (biological marker for stress) [42], individual practice, personal experience during the program, and facilitator feedback about adaptation of the MARS-A curriculum for the eHealth platform. The authors chose salivary cortisol levels as the biological marker for this study because of the possibility of using a noninvasive sampling method (ie, in comparison with blood tests) and based on promising, yet inconsistent reports of the effects of MBIs on cortisol levels and recommendations for future study [43]. They also chose cortisol in an attempt to reproduce the findings of a pilot study by [name] and colleagues [15] where reductions in cortisol levels during a mindfulness session had been shown to increase significantly pre- and post-MBI in a similar population of youth with chronic pain.

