### Data Analysis

Quantitative and qualitative data analysis will take place as described in Table 2. All quantitative analyses will be conducted using SPSS 24th edition (IBM Corp). Descriptive statistics will be used to identify participant demographics and disease characteristics. Quantitative self-report data will be analyzed using 1-way analyses of variance and analyses of covariance as well as paired *t* tests to assess pre-post MBI changes and to compare outcomes in the in-person versus eHealth arms as well as between the early versus wait-list control groups. A margin of 0.45 will be used as a prespecified noninferiority margin. For the primary outcome (mindfulness skills acquisition), the noninferiority question will be based on a confidence interval of 95% (2-sided) in relation to the noninferiority margin for the different treatment groups.

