## Discussion

### Anticipated Results

Based on previous pilot data collected by our team [11,15,23,25], we anticipate excellent levels of feasibility, acceptability, and satisfaction among participants in the in-person groups. In a study by [name] and colleagues [15] conducted in 19 adolescent females with chronic pain, using a similar MBI, the rate of attrition was low (17%), attendance was high (84%), and participants reported positive changes in the way they coped with their condition. We anticipate similar results in the eHealth groups, based on data from adult studies [18]. We hypothesize that both the in-person and eHealth modes of delivery will provide similar and significant improvements in mindfulness skills, mood, anxiety, self-esteem, and illness perception when compared to wait-list controls and that the magnitude of these effects will be correlated with the regularity of home practice. We project that participants in in-person and eHealth groups will have similar levels of home practice. In addition, we anticipate a significant reduction in pre-post session (5:30 PM to 7:00 PM) stress levels for both in-person and eHealth groups. Finally, we anticipate that all participants will see benefits of having incorporated mindfulness in their everyday life, such as improved level of functioning, sleep, or coping with illness, which will be captured by our semistructured interviews.

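### Cortisol is described only as a between-arm comparison of pre-post differences, and ANCOVA is assigned only to self-report data; unadjusted session-1 to session-8 changes would lose precision that adjustment keeps

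*Protocol article*

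**What the plan says.** The Data Collection section of the protocol article sets four saliva samples on each of two days; they "will be drawn at wake-up, at 12:00 PM, at 5:30 PM, and at 7:00 PM on the first and eighth (last) MBI session". Table 1 places those days at time 0 and week 8 for the early groups, and at weeks 8 and 16 for the wait-list groups. The same paragraph then gives the purpose: "This will allow for the comparison of pre-post cortisol level differences between participants in the in-person and eHealth arms". No other between-arm comparison of cortisol is described.

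The Data Analysis section says "Quantitative self-report data will be analyzed using 1-way analyses of variance and analyses of covariance", together with paired t tests. Cortisol is an immunoassay result (Table 2), so it falls outside that sentence, and no other sentence gives it a model.

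Elsewhere pre-post has other meanings. Outcome Measures explains the choice of cortisol by a pilot study in which "reductions in cortisol levels during a mindfulness session had been shown to increase significantly pre- and post-MBI", that is, a within-session drop compared before and after the programme. Anticipated Results says "we anticipate a significant reduction in pre-post session (5:30 PM to 7:00 PM) stress levels for both in-person and eHealth groups", which is a change within one session. The Intervention section, in its paragraph on the in-person groups, states: "Sessions will take place once a week after school from 5:30 PM to 7:00 PM". The last two samples of each day therefore bracket the session.

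Outcome Measures lists cortisol among the secondary outcomes. The protocol gives no cortisol SD, correlation, effect size or power.

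**The concern.** Read together, the two sections describe a change-score comparison for cortisol and reserve covariance adjustment for the questionnaires. A change score subtracts the whole session-1 value, however weakly it predicts the session-8 value. This has two effects.

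- **Noise.** When the correlation is low, subtracting a single-day sample adds more variation than it removes. With equal SDs, a change score at r below 0.5 is less precise than ignoring session 1 altogether.
- **Chance imbalance.** There are about 30 participants per arm and no stratification, so the arms may differ at session 1 by chance. A change score corrects for that difference with a slope fixed at 1, whatever the true slope is.

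The sample times raise a further problem. The 7:00 PM sample on the first day comes at the end of the first session, so it is not a pre-intervention value. A pre-post contrast that used it as baseline would subtract part of what the intervention may have done.

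At stake is the precision of the trial's only biological outcome, in a sample that the protocol itself calls small.

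**Working it through.** **Inputs.** From the protocol: 60 participants, half in each arm, so n=30 per arm (Power Calculations); attrition of 10% to 20% (Attrition and Compliance), so 24 per arm at 20%. The protocol has no cortisol figure to reproduce; its 80% power concerns the MAAS-A only. Assumed, because not given: r, the correlation between session-1 and session-8 values at the same clock time, and k, the ratio of the session-8 SD to the session-1 SD. Participants are treated as independent.

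**Step 1: variances with equal SDs (k=1), in units of SD².**
- Change score: 2(1-r) × 2/n
- ANCOVA: (1-r²) × 2/n, apart from a small-sample factor
- Ratio, ANCOVA to change score: (1-r²)/[2(1-r)] = (1+r)/2
- Information lost by the change score: 1 - (1+r)/2 = (1-r)/2

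| r | Information lost | 60 analysed by change scores are worth, by ANCOVA |
|---|---|---|
| 0 | 50% | 30 |
| 0.2 | 40% | 36 |
| 0.4 | 30% | 42 |
| 0.5 | 25% | 45 |
| 0.6 | 20% | 48 |
| 0.8 | 10% | 54 |
| 0.9 | 5% | 57 |

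A simulation with 30 per arm (20,000 runs) gave losses of 37.8%, 28.8%, 19.4% and 8.0% at r = 0.2, 0.4, 0.6 and 0.8. These are slightly below the formula because ANCOVA must estimate its slope.

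**Step 2: 95% confidence interval half-widths in SD units.** The ANCOVA variance carries the factor 1 + 1/(2n-4), which is 1 + 1/56 = 1.018 at n=30. With t of about 2.00:
- r=0.2: change 2.00 × √(1.6 × 2/30) = 0.65; ANCOVA 2.00 × √(0.96 × 2/30 × 1.018) = 0.51
- r=0.4: change 2.00 × √(1.2 × 2/30) = 0.57; ANCOVA 2.00 × √(0.84 × 2/30 × 1.018) = 0.48
- r=0.6: change 2.00 × √(0.8 × 2/30) = 0.46; ANCOVA 2.00 × √(0.64 × 2/30 × 1.018) = 0.42

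With 24 per arm, r=0.4 and t of about 2.01: change 2.01 × √(1.2 × 2/24) = 0.64; ANCOVA 2.01 × √(0.84 × 2/24 × 1.023) = 0.54.

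**Step 3: unequal SDs.** In units of the session-1 variance, the change score has variance 1 + k² - 2rk and ANCOVA has k²(1-r²). The first minus the second is 1 - 2rk + r²k² = (1-rk)², which is never negative. So in large samples the change score is never more precise, but the loss varies widely:
- k=1.3: 25% at r=0.2, 4% at r=0.6
- k=0.7: 61% at r=0.2, 52% at r=0.6

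**Step 4: chance imbalance.** With equal SDs, ANCOVA subtracts r times the session-1 difference and the change score subtracts all of it. One standard error of that difference is √(2/30) = 0.26 SD. At r=0.4 the two estimates then differ by (1-0.4) × 0.26 = 0.16 SD, through chance alone.

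**Step 5: which samples can be a baseline.** On the first day, wake-up and 12:00 PM precede the session. The 5:30 PM sample falls at its start and the 7:00 PM sample at its end. Allocation is disclosed by telephone before any of them.

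**The case against.** The strongest reply is that the cortisol sentence is a statement of purpose in Data Collection, not an analysis specification. It names no test and does not say raw or unadjusted; an ANCOVA of the difference on its starting value would fit it. Listing ANCOVA for self-report data does not forbid it for cortisol, and a condensed article may leave a biomarker model to an analysis plan that is not shown. This stands against any claim that the protocol rules out adjustment, which a reader might infer and the text does not support. It does not remove the point, because the article names the quantity to be compared and limits its covariance method to other outcomes.

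The second reply is that the intended contrast may be within-session, as Outcome Measures and Anticipated Results suggest. That is fair, and the session-1 to session-8 figures would then not apply directly. It adds to the need to define the term.

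The third is that a reader might take a loss of 20% to 40% as established. It is not: that range needs r between 0.6 and 0.2 and equal SDs, and the documents give neither.

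The fourth concerns the remedy. Session-1 samples follow disclosure of the arm, so anticipation could affect them and none is a pre-randomisation baseline. Adjusting for the 7:00 PM sample could remove part of an arm effect. Both objections stand and limit which samples should be used.

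**Conclusion.** The point holds conditionally. As written, the cortisol comparison is of pre-post differences, and the planned ANCOVA is not extended to it. If the differences are session-1 to session-8 changes and are left unadjusted, the loss of information is (1-r)/2 under equal SDs, from 50% at r=0 to 5% at r=0.9. With unequal SDs it can be larger or smaller. The direction is secure in large samples; the size cannot be fixed from the documents.

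A reader might go further and infer bias or a threat to the main result. Neither follows. Under randomisation an unadjusted change score is right on average, so the cost is precision and sensitivity to chance imbalance. Cortisol is a secondary outcome without a margin or power claim, and the primary noninferiority analysis of the MAAS-A is not affected. The change is worth making because the samples are collected anyway and the method is already in the plan.

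**What to change.** Extend the ANCOVA in Data Analysis to cortisol, and reword the Data Collection sentence to match:

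1. **Level contrast.** Compare session-8-day cortisol between arms, adjusted for the session-1-day value at the same clock time, using only samples taken before the session starts, such as wake-up and 12:00 PM. Do not use the session-1 7:00 PM sample as a baseline.
2. **Within-session response.** Compare the 7:00 PM value between arms, adjusted for the 5:30 PM value, and say on which day or days.
3. **Definition.** State which of these contrasts pre-post means wherever the term is applied to cortisol.
4. **Caveat.** Note that session-1 samples are taken after the arm is disclosed, so anticipation could affect them. By session 8 the 5:30 PM value also follows seven sessions, so the within-session result is conditional on the level at the start of that session.

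Unadjusted differences can still be reported descriptively. The cost is a few sentences of wording: no new samples, no extra participants and no new method.
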